### c. Methods of data collection

An outline of data collection methods is provided for demographic, primary and secondary outcomes and potential confounding variables. Detailed information including the variables are provided in (Attachment 14). Table 3 provides a summary of data collection. Data collection procedures are described thereafter.

## **Data collection timepoints for the primary outcomes**

For the entire study there are seven points in time at which data will be collected. These are labelled T0 (baseline), T1 – T6 in Figure 4 and are referred to in the below outline of data collected. Reason for the training program data collection timepoints are as follows:

- T0- Baseline - groups A & B
- T1 - Measure Effect of Peer Support Network - 6 Months Post Baseline Group A & B (Aboriginal Health Workers and Practitioners only).
- T2 – Measure effect of training program (PSN, Online Modules, Onsite Support) on group A - 8.5 Months post-baseline (data collected on both group A & B).
- T3 – Baseline of group B prior to doing the intervention (data collected on both group A & B), 14.5 months post-baseline.
- T4 – Measure effect of training program (PSN, Online Modules, Onsite Support) on group B post group B undertaking the intervention at 17 months from baseline (data collected on both group A & B).
- T5 – Sustainability of effect of training program on group A 23 months post-baseline, and group B 6 months post commencement of intervention.
- T6 - Sustainability of effect of training program on group A 29 months post-baseline, and group B 12 months post commencement of intervention.

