### **The Intervention: Aboriginal Diabetes Workforce Training Program (training program)**

The training program consists of 3 components (Figure 1):

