### **3. AIM & OBJECTIVES**

#### **Aim**

To evaluate the effectiveness of a culturally and contextually informed Aboriginal Diabetes Workforce Training Program (hereafter training program) on Aboriginal primary health care workforce knowledge, attitude, confidence, skill and practice relating to diabetes care.

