## Randomisation

Randomisation will occur at the service level. Enrolled health services will be randomised into Group A and Group B. Randomisation and allocation will be undertaken after six months of providing PSN for all enrolled health service sites and prior to commencement of the training program. All enrolled health service sites will be listed, and a statistician will be responsible for randomizing the health service sites into cluster one (Group A participants) or cluster two (Group B participants) using a block size through a computer program for randomisation.

For the intervention assignment; a cluster crossover randomised trial will be employed in this study, as all participants receive the same intervention based on random service site allocation. Participants in the study sites will know which group they have been allocated after completing six months of the PSN, and before commencing the E-Learning module for group A. The project research team will not be blinded to group A or B allocation, only people analyzing the results will be masked/blinded.

**Peer Support Network (months 1-17):** Only AHW/Ps will participate in the PSN. AHW/P participants from both Group A and Group B will participate in the PSN for the entire duration of the study. The PSN will commence and convene for 6 months prior to Group A doing the e-learning modules and the OS. The PSN will run online via Teams, once a month, for 1.5 to 2 hours duration, and will be facilitated by a credentialed diabetes educator (DNE) who is a research team member.

As this is a pragmatic trial, it is understood that AHW/Ps may not be able to attend all PSN sessions due to competing work and/or personal priorities.

The PSN meetings will not be recorded. The PSN Facilitator will record participation in the network.

**E-Learning Modules (10 weeks):** There are 9 self-paced e-Learning modules. Each module takes approximately 1 hour to complete. Ten weeks have been allocated to complete the e-learning modules. All participants will do the e-learning modules. Services will have agreed to allow their staff to use the work computers and internet and to do the modules during work hours. These can also be done from any computer, at any time. The modules can be left and picked up at the same place for convenience during working hours.

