#### **Primary outcomes**

Directed Acyclic Graphs (DAGs) are being used to determine variables that need to be collected to adjust for potential confounding within statistical models. DAGs enable the conceptualisation of causal pathways. A DAG has been done for each primary outcome.

Generalized linear mixed effects models (GLMMs) with compound symmetric (exchangeable) correlation structure will be used to account for within health care centre (cluster) correlation; logit or log link will be used for binary outcomes such as prevalence resulting in mixed effect logistic regression, while log link will be used for count outcomes resulting in mixed effects negative binomial regression. GLMMs are a missing data method only assuming missing at random – MAR (instead of the more stringent MCAR – missing

completely at random). Effect measures will also be presented through calculation of number needed to treat and its associated 95% confidence interval. Analysis after the 12-month intervention follow-up is planned, spending  $\alpha=0.005$ .

In addition, a descriptive pre-post analysis of survey results due to participating in the PSN alone in the first six months will be calculated using appropriate parametric or non-parametric tests. These analyses will occur after each collection timepoint.

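### Both groups get the Peer Support Network, so the randomised comparison at T2 estimates e-learning plus onsite support, not the three-part programme; at T4 it isolates neither

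*Protocol*

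**What the plan says.** The section on the intervention states that "The training program consists of 3 components": the PSN, nine e-learning modules and onsite support. The Introduction says that a cluster randomised design at service level will evaluate this programme, and the Aim is "To evaluate the effectiveness of a culturally and contextually informed Aboriginal Diabetes Workforce Training Program".

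Under the data collection timepoints for the primary outcomes, T2 (8.5 months) is to "Measure effect of training program (PSN, Online Modules, Onsite Support) on group A" and T4 (17 months) is to "Measure effect of training program (PSN, Online Modules, Onsite Support) on group B". Both collect data from both groups.

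The Randomisation section says "Only AHW/Ps will participate in the PSN", that "AHW/P participants from both Group A and Group B will participate in the PSN for the entire duration of the study", and that "The PSN will commence and convene for 6 months prior to Group A doing the e-learning modules and the OS". Services are randomised after those six months, a moment which the same section places before the training programme starts. The PSN then continues in both groups through each 10-week training block and the washout.

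For the PSN itself, the Primary outcomes part of Data Analysis plans "a descriptive pre-post analysis of survey results due to participating in the PSN alone in the first six months". The stated purpose of T1 is to measure the PSN's effect.

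**The concern.** A randomised comparison can attribute to treatment only what differs between the groups. The PSN never differs between them: AHW/Ps have it in both and multidisciplinary staff have it in neither. The design set out in the Introduction therefore cannot deliver the effect that the T2 and T4 entries name.

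The Protocol also uses two definitions of the programme. The T2 and T4 entries include the PSN. The Randomisation section excludes it, since six months of PSN have passed when the programme is said not to have begun. The T3 entry also excludes it by calling 14.5 months a pre-intervention baseline for Group B, whose AHW/Ps have by then had the PSN throughout.

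If this is left as it is, a two-component effect could be reported as that of three components, or an uncontrolled before-after change could be read as the trial's randomised result. Pooling staff types also mixes two contrasts: training added to the PSN, and training against no programme component.

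**Working it through.** The Protocol gives no figure for this contrast to reproduce, so the check tabulates exposure, applies simple algebra and then counts hours.

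**1. Exposure by group** (Randomisation, the Group A, washout and Group B paragraphs, and the timepoint list; OS = onsite support)

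| Time | AHW/P, A | AHW/P, B | Multidisciplinary, A | Multidisciplinary, B |
|---|---|---|---|---|
| T0 | none | none | none | none |
| T1, 6 mo | PSN | PSN | none | none |
| T2, 8.5 mo | PSN + modules + OS | PSN | modules + OS | none |
| T3, 14.5 mo | PSN + earlier modules and OS | PSN | earlier modules and OS | none |
| T4, 17 mo | PSN + earlier modules and OS | PSN + modules + OS | earlier modules and OS | modules + OS |

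After T0, no timepoint has a randomised group of AHW/Ps without the PSN.

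**2. What A versus B estimates.** Let P be the PSN effect, E the effect of modules plus OS, and r the share of E that Group A still holds at T4. Effects are taken as additive. The values are assumptions for illustration; the Protocol gives none.

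- T2, AHW/Ps: A - B = (P + E) - P = E. With E = 0.5 SD and P = 0, 0.25, 0.5 or 1.0 SD, A - B is 0.5 SD every time. The three-part effect against nothing, P + E, would be 0.5, 0.75, 1.0 or 1.5 SD.
- T2, multidisciplinary staff: A - B is modules plus OS against no component. This effect need not equal E in AHW/Ps.
- T3: the same contrasts, six months later (14.5 - 8.5), so persistence.
- T4, AHW/Ps: B - A = (P + E) - (P + rE) = (1 - r)E. With E = 0.5 SD this is 0, 0.25 or 0.5 SD for r = 1, 0.5 or 0. Group A finished about 17 - 8.5 = 8.5 months earlier, so this compares recent with earlier training.

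**3. Where P can appear.** Only in changes within a group: T0-T1 (PSN), T0-T2 in Group A and T0-T4 in Group B (whole programme, AHW/Ps only). None has a concurrent control, and all carry time trends and repeat testing. In Group A's T0-T2 change, 6/8.5 = 71% of the interval precedes randomisation.

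**4. AHW/P hours outside the contrast at T2**

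- PSN: about 8 monthly sessions of 1.5-2 h (Randomisation) = 12-16 h.
- Modules: 9 x 1 h = 9 h. OS: 2-6 h (Table 2). Together 11-15 h.
- Lowest share: 12/(12 + 15) = 44%. Highest share: 16/(16 + 11) = 59%.

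**The case against.** The strongest reply is that giving a shared background component to both groups is a legitimate add-on design, and that the Protocol is open about it. The effect of modules plus onsite support remains randomised and interpretable at T2. That stands: the point concerns what the result is called, not the design.

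It is also true that the T2 and T4 entries never say that they rest on the A-versus-B contrast, that the Aim and Hypothesis list no components, and that an analysis plan not seen here may name the contrast. But if T2 and T4 are read as changes within a group, the whole-programme effect is uncontrolled and the Introduction's randomised evaluation still does not deliver it. No analysis plan can recover a randomised PSN effect from this allocation.

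A reader might infer more than the text supports:

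- **That the PSN is presented as tested under randomisation.** It is not. It has its own timepoint, and its analysis is already called descriptive and pre-post. Only the attribution of the change to the PSN goes too far.
- **That about 70% or more of programme hours lie outside the contrast.** Table 2's 17 x 2 h = 34 h against 11-15 h gives 34/49 = 69% to 34/45 = 76%. That counts sessions after T2 and uses only the longest session length.
- **That multidisciplinary staff could serve as a control for the PSN.** That comparison would be non-randomised and confounded by profession. It also needs their T1 data, on which the timepoint list (AHW/Ps only) and Table 3 (all participants) conflict.

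**Conclusion.** The point holds as a mismatch between the effect that the Protocol says it will measure and the effect that its randomisation can identify. At T2, and as persistence at T3, the randomised effect is that of e-learning plus onsite support: added to the PSN in AHW/Ps, and without it in multidisciplinary staff. It would be tempting to say the same of T4, but there A versus B isolates neither the three-part nor the two-part effect. PSN and whole-programme effects are non-randomised changes.

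That the PSN is common to both groups follows from the allocation and needs no numerical assumption; its exact cancellation in the algebra assumes additive effects. Without additivity, T2 still gives only the effect of training in people who already have the PSN. The 44-59% range assumes about eight sessions, all attended, and applies to AHW/Ps only; the Protocol expects some missed sessions. It says nothing about how much of any benefit comes from the PSN.

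This should be fixed because it changes what the trial may conclude. It does not invalidate the T2 comparison.

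**What to change.** - In the Aim, the Hypothesis and the T2 purpose, state the randomised effect as that of e-learning plus onsite support, on top of the PSN for AHW/Ps and without the PSN for multidisciplinary staff.
- Report that effect by staff type beside the pooled estimate.
- Relabel T4 as a change within Group B or as a comparison of recent with earlier training.
- Use one definition of the programme throughout, including where the Randomisation section places allocation before the programme starts.
- Label T0-T1, T0-T2 in Group A and T0-T4 in Group B as non-randomised pre-post changes.
- Replace the causal wording about the PSN in the T1 purpose and in the Primary outcomes part of Data Analysis with neutral wording, such as change over the first six months.

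Allocation, sample size and data collection stay as they are. The costs are a narrower claim and imprecise staff-type estimates: the Protocol plans for 40 participants and, after 50% drop-out, 40 x 0.5 = 20 completers. These estimates should be presented as descriptive, with intervals.

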**Onsite Support (minimum of twice over 10-week period):** The OS sessions will occur during the same 10-week period as the e-Learning modules. The OS will be face to face at the primary health care service. The number of OS sessions and what is covered during them will be negotiated between the participants and the OS Facilitator. It is suggested that each service hold a minimum of 2 sessions with the OS Facilitator. OS sessions will be held as a group, if there is more than one AHW/P or multidisciplinary health care providers within the health service. The group sessions will be held with AHW/Ps for the first half of the session and then include multidisciplinary health care providers for the remainder of the session. This format will be assessed and adapted as needed. This format responds to direct feedback during the co-design of the training program.

The OS will be facilitated by a credentialed diabetes educator (CDE) employed by Diabetes SA. The CDE will be a member of the research team.

**Group A:** At the start of month 7, AHW/P and multidisciplinary health care provider participants within the health services randomised to Group A will commence the e-Learning modules and OS, for a duration of 10 weeks. During this time, AHW/Ps from both Group A and Group B will continue to participate in the PSN.

**Wash out period (6 months):** There is a six month 'wash out' period where only the PSN is running. This will occur between Group A and Group B doing the e-Learning modules and participating in the OS.

**Group B:** After the 6-month washout period the participating AHW/Ps and multidisciplinary health care providers within the health services randomised to Group B will commence the e-Learning modules and OS, for a duration of 10 weeks. During this time, AHW/Ps from both Group A and Group B will continue to participate in the PSN.

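### Sustainability is tied to T5 and T6, when both groups are trained, while T3, the only delayed trained-versus-untrained randomised comparison, is named only as Group B's baseline

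*Protocol*

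**What the plan says.** Protocol, Randomisation: "Randomisation will occur at the service level". Group A's services train first, for 10 weeks beginning at month 7, with e-learning and onsite support together. Afterwards, "There is a six month 'wash out' period where only the PSN is running". Group B's turn is fixed by this sentence: "After the 6-month washout period the participating AHW/Ps and multidisciplinary health care providers within the health services randomised to Group B will commence". Its block also lasts 10 weeks. The PSN (Peer Support Network, for Aboriginal Health Workers and Practitioners only) runs in both groups throughout.

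Protocol, Data collection timepoints for the primary outcomes, opens with "Reason for the training program data collection timepoints are as follows". The relevant entries are:

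- The T2 visit, at month 8.5, looks at the programme's effect in Group A; both groups are surveyed.
- The T3 visit has one stated reason: "Baseline of group B prior to doing the intervention (data collected on both group A & B), 14.5 months post-baseline".
- Month 17 is T4, for the effect in Group B; again both groups are surveyed.
- The T5 visit has this reason: "Sustainability of effect of training program on group A 23 months post-baseline". Group B is covered in the same way.
- Month 29 is T6, with the same purpose as T5.

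The Data Analysis section plans mixed models and dates one analysis, after 12-month follow-up. It names no A-versus-B contrast at any visit.

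**The concern.** At T3 both randomised groups are surveyed. Group A finished training six months earlier, and Group B has had neither e-learning nor onsite support. That is a direct randomised look at how much of the effect is retained, yet T3's stated reason covers only its use as Group B's starting value. Calling the preceding interval a wash-out reinforces this, because it treats a retention period as a gap.

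The visits that carry the sustainability label have no untrained comparator. A reader who follows the timetable will look for lasting effect there, either in A-B at T5 and T6 or in change from T0. The first can be zero when the effect has lasted fully. The second mixes retention with repeat testing, the PSN and calendar drift. A T3 contrast chosen after the results are known, among five primary outcomes and seven visits, would be weaker evidence than one named now.

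**Working it through.** **Calendar.** Inputs are the training dates under Randomisation and the timepoint list. Ten weeks is 70/30.4375 = 2.30 months. From a start at 6.0 months: end of A's training 8.30 (stated 8.5); plus 6 gives 14.30 (14.5); plus 2.30 gives 16.60 (17); plus 6 gives 22.60 (23); plus 6 gives 28.60 (29). The stated times reproduce to within half a month.

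**Months since completing training**, taking completion as 8.5 (A) and 17 (B):

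| Visit | Month | Group A | Group B |
|---|---|---|---|
| T2 | 8.5 | 0 | untrained |
| T3 | 14.5 | 6 | untrained |
| T4 | 17 | 8.5 | 0 |
| T5 | 23 | 14.5 | 6 |
| T6 | 29 | 20.5 | 12 |

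The protocol dates Group B's T5 and T6 as 6 and 12 months from commencement. By its own calendar those intervals run from completion; from commencement they are 23 - 14.5 = 8.5 and 29 - 14.5 = 14.5 months. The table uses completion.

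**What A-B shows.** Let d be the effect at completion, the same in both groups, decaying with half-life h (assumed; the protocol gives none). Then A-B = d × (0.5^(tA/h) - 0.5^(tB/h)), with B's term 0 while B is untrained.

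| Half-life | T3 | T4 | T5 | T6 |
|---|---|---|---|---|
| no decay | d | 0 | 0 | 0 |
| 12 months | 0.71d | -0.39d | -0.27d | -0.19d |
| 6 months | 0.50d | -0.63d | -0.31d | -0.16d |

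Example, h = 12 at T5: 0.5^(14.5/12) - 0.5^(6/12) = 0.433 - 0.707 = -0.27. Full persistence and no effect at all both give 0 from T4 on; only the T2 result separates them. T3 separates them by itself.

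**Change from T0.** If all scores drifted up by 0.01 to 0.02 SD per month (assumed), the T0-to-T5 change would contain 23 × 0.01 = 0.23 to 23 × 0.02 = 0.46 SD that is not retention. A-B at T3 removes any drift common to both groups, whatever its size.

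**Precision at T3.** Inputs: 40 enrolled and 20 completers (Sample); up to 17 services (Waiver of consent). Assumed: equal groups, two-sided 0.05, 80% power, ICC 0 to 0.2. Detectable difference in SD = (1.96 + 0.84) × √(2 × DE/n), with DE = 1 + (m - 1) × ICC.

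- n = 10 per group, m = 20/17: 1.25 to 1.27 SD.
- n = 20 per group (no dropout), m = 2: 0.89 to 0.97 SD.

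If only 0.50d remains at T3, d itself would have to be about 0.89/0.50 = 1.8 to 1.27/0.50 = 2.5 SD to be detected.

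**The case against.** The strongest reply is that nothing is lost. The primary outcomes are collected from both groups at T3, the timetable does not say T3 serves one purpose only, and a mixed model over all visits could yield the contrast. Visit contrasts are commonly left to an SAP, which was not available here. This stands as far as it goes: a reader might infer that the trial discards the comparison, and the protocol does not say so. What remains is that the protocol itself assigns the sustainability question to visits, and omits the one with an untrained comparator.

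Three other stronger readings are tempting and are not supported:

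- *T3 is the only randomised test of whether the effect lasts.* It is not. A-B at T4, T5 and T6 still compares randomised groups. Given an effect at T2 and a similar training effect in both groups, a negative A-B indicates decay and a zero indicates no differential decay.
- *Sustainability will be judged on uncontrolled data.* The protocol does not say whether it will use A-B or change from T0. Only the latter is uncontrolled. Barring between-group use of T5 and T6 would discard real information, including all the data beyond T4.
- *T3 is free of confounding.* The modules are already free to use (Ethical Considerations), all participants are invited to one Teams site, allocation is known to participants, and 50% dropout is allowed for. The contrast is randomised but exposed to contamination and differential attrition.

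It is also fair that T3 reaches only six months, and that the lack of a later untrained comparator follows from training every service.

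**Conclusion.** The point holds in a limited form. T3 is the only delayed comparison of trained with not-yet-trained randomised services, and the protocol gives that comparison no role while placing sustainability at T5 and T6. The size of the gap is clearest without decay: A-B is d at T3 and 0 at both labelled visits. This rests on the stated calendar and on equal training effects in the two groups; the half-lives and drift are illustrations.

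The T3 contrast concerns e-learning plus onsite support. For Aboriginal Health Workers and Practitioners the PSN runs in both groups; multidisciplinary providers do not take part in it. T3 says nothing about 12 months or later, and its precision will be low. Naming it settles its role, not its power.

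**What to change.** In the timepoint list, add a second purpose to T3: *randomised comparison of Group A (six months after training) with Group B (not yet trained): effect of e-learning plus onsite support retained at six months*. Estimate it with the same model as T2, and order it after T2. Use surveys completed before Group B's modules open. Surveys stay open for 14 days, so scheduling the T3 window to close before that date would avoid excluding late responders.

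For T5 and T6, state that they describe longer-term follow-up by time since training without an untrained comparator, and that A-B differences there are read as differences in time since training, not as the training effect.

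The change needs protocol wording and no new visit, survey or participant. It adds one comparison for each of the five primary outcomes. Because precision is low and attrition and contamination are likely, the protocol should also say that a null T3 result is not evidence that the effect was lost.
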